#### Functional Outcome Measures

The effects of the prosthetic devices and the rehabilitative intervention on physical performance will be evaluated using agility and mobility tests, including the 6-minute walk test (6MWT) [58], the Amputee Mobility Predictor with prosthesis (AMPpro) [59], and the Comprehensive High-Level Activity Mobility Predictor (CHAMP) [60]. By capturing the functional measures in each group, the effects of the ankle-foot device can be isolated from the rehabilitation effects on physical performance. These measures are as follows:

6MWT: the 6MWT measures the distance an individual can walk in 6 minutes without help or encouragement. It is a valid and reliable measure that correlates with physical function and has good interrater and intrarater reliability in individuals with lower limb loss [58].AMPpro: the AMPpro is a 21-item instrument designed to measure prosthetic mobility in individuals with lower limb loss [59].CHAMP: participants who attain a score of 37 or higher on the AMPpro will undergo the CHAMP, which consists of the following tasks:Single limb stance: participants fold their arms across their chest and then lift their foot above a 15-cm cone or box. The test ends when the foot touches the ground again (or until 30 s) or if the arms uncross. This procedure is performed on both feet.Edgren Sidestep Test: participants sidestep left and then right along a 5-meter line of cones (1 meter apart). The sidestep test lasts for 10 seconds.T-Test: the T-Test measures forward, lateral, and backward walking (or running) and sidestepping in a T pattern.Illinois Agility Test: this advanced agility test requires the participant to run or walk and change direction around multiple cones. Over 60 meters, participants perform 90° and 180° turns 11 times around multiple cones.

#### Powered Ankle-Foot Prosthesis Fitting

Following all baseline data collection procedures, all participants will then be fit with the Empower. Study prosthetists at VANYHHS, WRNMMC, and JAHVH are highly experienced in fitting all commercial microprocessor knees and the Empower. The study prosthetists will bench align the powered ankle-foot device onto the participant’s existing microprocessor prosthetic knee and socket. Once the powered ankle-foot device is fitted and bench-aligned to the prosthetic knee and socket, dynamic alignment of the prosthetic knee and ankle will occur. Initially, the study prosthetist will ensure proper alignment of the microprocessor prosthetic knee with the Empower turned off. The Empower will still function (ie, articulate) with the power off but will not provide net positive plantarflexion torque. The microprocessor prosthetic knee software and prosthesis alignment will be adjusted during standing and walking tasks, as necessary, until the prosthetist and the participant are satisfied with the knee alignment. Once the microprocessor knee setup is completed, the Empower will be powered on and adjusted according to the manufacturer’s specifications. Briefly, the participants will sequentially walk at 3 different speeds (slow, self-selected, and fast) while the stiffness and power delivery of the powered ankle-foot device is tuned [33]. If further dynamic adjustments to prosthetic knee alignment are necessary, these adjustments will be made at this point.

#### Powered Ankle-Foot Device Standard of Practice

Once a stable and comfortable alignment has been established, all participants will be educated by the study prosthetist on the proper use of the Empower, which includes battery handling and charging, understanding low battery indicators, considerations while driving with the Empower (if applicable), and avoidance of exposure to rain and water. Next, the participants will ascend and descend an Americans with Disabilities Act–compliant ramp under the supervision of the study physical therapist or prosthetist. The intent of ramp walking is to trigger the power for ascent but not during descent. Each participant will be given the opportunity to practice the ramp as often as necessary to ensure safe and comfortable use. The participants will then negotiate a standard staircase with handrails under the supervision of the study physical therapist or prosthetist to ensure that they can safely negotiate stairs using the Empower. Proper technique will consist of demonstrating the correct foot placement on each step to activate powered push off during ascent. Participants unable to ascend stairs in a step-over-step pattern will be shown the correct foot placement using a step-to gait pattern. For proper stair descent, participants will be shown the correct foot placement to initiate rollover and not trigger the power. Participants will be given time to practice stair ascent and descent. After stair and ramp ambulation, participants will be asked to demonstrate safe use of the Empower in different situations, including turning, varying speeds, sudden stops, obstacle avoidance, stepping over obstacles, and different surfaces. Once the physical therapist is satisfied that the participant has demonstrated safe use and all questions have been answered, the participant will be released home with the Empower. If the physical therapist feels that the progress is unsatisfactory, the participant will not take the Empower home and will be asked to return for continued supervised use until the participant demonstrates safe use. The standard of practice to use the powered prosthesis is approximately 30 to 45 minutes after fitting and tuning.

Following the baseline visit, group A will undergo the device-specific PT program, whereas group B will not undergo any further training.

### PT Program: Group A

#### Overview

Participants in group A will complete, on average, 8 PT sessions lasting 30 to 45 minutes each. The exact PT protocol and criteria for advancement are outlined by level in the subsequent section. In brief, level 1 of the PT plan will focus on education, strengthening through therapeutic exercises, and early neuromuscular reeducation. A home exercise program (HEP) will be initiated during the initial sessions and will progress along with the program. Level 2 will include gait training on level surfaces, sit-to-stand transitions, and ramp negotiation. Level 3 will include multidirectional training for both neuromuscular reeducation and gait and the introduction of stair ascent and descent. Training will conclude with level 4 where the previous skills will be further challenged and advanced gait skills, including ambulation on ramps and uneven surfaces, will be introduced. Participants must meet the outlined criteria before progressing through each level. Participants who do not meet the specified criteria will be offered additional PT sessions. The number of additional sessions will be recorded and used to refine the PT program for future use.

#### Level 1 (Sessions 1 and 2)

Level 1 (Table 1) includes initial evaluation, patient education, gait assessment, training to ensure safe use in the community, therapeutic exercises (including introduction of the HEP), and the initiation of early neuromuscular reeducation training.

**Table 1 table1:** Level 1 device-specific physical therapy protocol.

Protocol		Description	Criteria for advancement to level 2
**Level 1 (sessions 1 and 2)**			
	Evaluation	Assessment of prosthesis fit and gait to determine deficits	N/A^a^
	Strengthening	Strengthening of transversus abdominis and multifidus, gluteus maximus, gluteus medius, and general trunk strengthening	Able to perform HEP^b^ independently
	Stretching	Address deficits from evaluation, including iliopsoas	Within normal limits for range of motion
	Education	Explanation of function of powered ankle-foot device	Verbalizes understanding of function of powered ankle-foot device
	Gait training	Safely negotiate level surface without increased falls or stumbles	Able to ambulate 46 meters without an assistive device independently on a flat, level surface; self-reported occurrence of stumbles or falls is no greater than baseline
	Mobility training	Side stepping, backward stepping, and turns	Able to ambulate outdoors without increased falls or stumbles with or without an assistive device
	Neuromuscular reeducation	Weight shifting and control over prosthesis, intact limb mobility (toes in and toes out, heel in and heel out) to promote weight shifting, static single limb balance training on prosthesis side with upper limb support, and anterior and posterior stepping exercises with the intact limb	Independent in HEP
	HEP	Initiated with all therapeutic exercises outlined in level 1	Independent in HEP

^a^N/A: not applicable.

^b^HEP: home exercise program.

#### Level 2 (Sessions 3 and 4)

Level 2 (Table 2) will include the progression of therapeutic exercises through increased frequency, duration, and resistance.

All strengthening and stretching will be shifted to the HEP by the completion of level 2. Lumbar, abdominal, and closed kinetic chain lower extremity strengthening exercises will progress to more dynamic positions. Single limb stance progressions (neuromuscular reeducation) will include decreased upper limb support for stepping exercises and progressing to step touches with the intact limb. Upper limb support will progress from bilateral support to support provided only on the side of the prosthesis. Anterior and posterior stepping exercises will begin with the support of parallel bars while maintaining weight on the prosthesis.

**Table 2 table2:** Level 2 device-specific physical therapy protocol.

Protocol		Description	Criteria for advancement to level 3
**Level 2 (sessions 3 and 4)**			
	Evaluation	Reassessment as needed	N/A^a^
	Strengthening	Progression to sitting, quadruped, planks, standing, and transitions	Independent in HEP^b^
	Stretching	Primarily used for cooldown at completion of each session	Independent in HEP
	Education	Description of HEP and purpose of each exercise	Verbalizes understanding of each exercise
	Gait training	Improving step length symmetry (eg, verbal cueing to increase step length on nonprosthesis side) and improving rollover on prosthesis side (eg, resistive gait training with TheraBand)	Ability to trigger power in prosthetic foot during gait >50% of steps and increased gait symmetry with verbal cueing for step length as determined through observational gait analysis
	Mobility training	Transfers (eg, stand-to-sit), and ramp negotiation	Able to maintain midline center of mass with stand-to-sit transfer
	Neuromuscular reeducation	Intact limb mobility (eg, rolling ball under intact limb) to promote weight shifting, static single limb balance training on prosthesis side with minimally necessary upper limb support and stepping exercises (eg, step touches 15-20 cm step in parallel bars and step touches to a cone in the parallel bars)	Independent in HEP
	HEP	Includes therapeutic exercises outlined in level 2	Independent in HEP

^a^N/A: not applicable.

^b^HEP: home exercise program.

#### Level 3 (Sessions 5 and 6)

At level 3 (Table 3), all strengthening will be performed exclusively in the HEP. PT will include neuromuscular reeducation progression, including multidirectional movements.

Stepping exercises will be performed with decreasing upper extremity support at a tolerance demonstrated by the participant maintaining an appropriate body position. Single limb stance activities will include perturbations, such as resistance with movements of a non–weight-bearing intact limb or standing on a foam pad or balance disc. Gait training will include multidirectional stepping with upper extremity support in the parallel bars. Resistive gait training will be introduced to promote proper mechanics for loading the prosthesis in stance and achieving maximal energy return at push off. In addition, manual proprioceptive neuromuscular facilitation will be performed to promote proper anterior pelvic rotation. Multidirectional ambulation will be progressed to outside of parallel bars.

**Table 3 table3:** Level 3 device-specific physical therapy protocol.

Protocol		Description	Criteria for advancement
**Level 3 (sessions 5 and 6)**			
	Evaluation	Reassessment as needed	N/A^a^
	Strengthening	Review as needed	Independent in HEP^b^
	Stretching	To be used for cooldown at session completion	Independent in HEP
	Education	Gait training and purpose for improving symmetry	Verbalizes understanding of gait training
	Gait training	Promoting gait initiation on prosthesis side with anterior pelvic rotation (ie, manual techniques to facilitate or initiate anterior pelvic rotation while in parallel bars with progression to anterior stepping on prosthesis side), relaxed upright posture with ambulation (ie, verbal cueing to keep chest upright), and resistive gait training with TheraBand and verbal cues for increased step length with intact limb	Demonstrates ability to trigger power with at least 80% accuracy during level ground ambulation and increased gait symmetry, including upright posture, step length, and toe break as determined through observational gait analysis
	Mobility training	Ramp and stair negotiation	Hill Assessment Index score ≥6 (ie, step past more than half foot length, with assistive device)
	Neuromuscular reeducation	Four-directional resistance exercise on intact side while maintaining single limb stance on prosthesis side, static single limb balance training on prosthesis side to be progressed to noncompliant surface (eg, foam), and progression of stepping exercises to increase time in single limb stand on the prosthesis	Able to maintain single limb stance on prosthesis side with or without an assistive device for 15 seconds
	HEP	Includes therapeutic exercises in level 3	Independent in HEP

^a^N/A: not applicable.

^b^HEP: home exercise program.

#### Level 4 (Sessions 7 and 8)

At level 4 (Table 4), PT will include advanced neuromuscular reeducation and gait training, followed by a final PT evaluation.

Neuromuscular reeducation will include single limb squats in the parallel bars with upper extremity support, as needed. Gait training will continue resistive training on even surfaces, proprioceptive neuromuscular facilitation for pelvic rotation, verbal and tactile cueing for symmetrical and appropriate trunk rotation, and negotiation of uneven surfaces.

Individuals who do not meet the criteria to complete the PT program will be offered an additional 8 PT sessions after completion of the study.

**Table 4 table4:** Level 4 device-specific physical therapy protocol.

Protocol		Description	Criteria for advancement
**Level 4 (sessions 7 and 8)**			
	Evaluation	Re-evaluation at final session	N/A^a^
	Strengthening	N/A	N/A
	Stretching	To be used for cooldown at session completion	Independent in HEP^b^
	Education	Importance of continuation of HEP	Verbalizes understanding
	Gait training	Promoting gait initiation on prosthesis side with anterior pelvic rotation, manual techniques and verbal cues to promote increased trunk rotation and trunk rotation symmetry, verbal cueing for symmetrical arm swing and trunk rotation (eg, “relax your shoulders”), and resistive gait training with TheraBand and verbal cues for increased step length with the intact limb and relaxed upright posture	Demonstrates ability to trigger power with at least 90% accuracy for powered prosthetic foot and increased gait symmetry for trunk rotation and arm swing, as determined through observational gait analysis
	Mobility training	Ascending and descending ramps and stairs	Stair Assessment Index score of at least 4 (with assistive device, step-to pattern) for ascending and descending stairs, and ambulates in the community without increased participant-reported stumbles or falls compared with baseline
	Neuromuscular reeducation	Applied during HEP	Demonstrates increased gait symmetry for step length, push off, anterior pelvic rotation, upright posture, trunk rotation, and arm swing
	HEP	Review HEP	Demonstrates independence in HEP

^a^N/A: not applicable.

^b^HEP: home exercise program.

### Data Collection Visit 2

After completion of the device-specific PT program, all participants will undergo data collection on the powered ankle-foot prosthesis. The participants will repeat the quality-of-life assessment, subjective surveys, pain assessment, cognitive load assessment, biomechanical gait analysis, and functional measures using the powered ankle-foot prosthesis, as described in the baseline visit. Following visit 2, participants will keep the powered ankle-foot prosthesis for an additional 4 weeks of home use and community use but will not undergo any further device-specific training.

### Data Collection Visit 3

After the final 4 weeks of powered ankle-foot prosthesis use, participants will undergo final data collection. Participants will repeat the quality-of-life assessment, subjective surveys, pain assessment, cognitive load measurements, neurocognitive assessment, biomechanical gait analysis, and functional measures, as described in the baseline visit. Following data collection, all participants will be refitted with their energy storing and returning ankle-foot devices, and the powered ankle-foot devices will be returned to the study staff.

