**Methods:**

This prospective, multisite study will enroll 30 individuals with unilateral transfemoral limb loss. At baseline, participants will undergo a full gait analysis and assessment of function, neurocognition, cognitive load, subjective preferences, and pain using their current passive prosthesis. The participants will then be fitted with a powered ankle-foot device and randomized into 2 equal groups: a powered device with a device-specific rehabilitation intervention (group A) or a powered device with the current standard of practice (group B). Group A will undergo 4 weeks of device-specific rehabilitation. Group B will receive the current standard of practice, which includes basic device education but no further device-specific rehabilitation. Data collection procedures will then be repeated after 4 weeks and 8 weeks of powered ankle use.

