## Methods

### Study Overview

This investigation will be a prospective, multisite study including VA New York Harbor Healthcare System (VANYHHS), James A. Haley Veterans’ Hospital (JAHVH), and Walter Reed National Military Medical Center (WRNMMC). Enrollment began in September 2018, and data collection is expected to conclude in 2024. Briefly, 30 individuals with transfemoral limb loss are expected to be enrolled equally across the 3 sites. For all participants, a full biomechanical gait analysis, functional measures, surveys, neurocognitive assessment, cognitive load assessment, and pain assessment will be captured at baseline with their clinically prescribed passive energy storing and returning ankle-foot prosthesis. The participants will be fitted with a powered ankle-foot device (Empower) and then be evaluated for safe use. The participants will then be randomly assigned into 2 groups: a powered ankle-foot device with a 4-week, 8-session device-specific PT intervention (group A) or a powered ankle-foot device with the current standard of practice (group B), which includes basic device education and training provided by the study prosthetist (outlined in the Powered Ankle-Foot Device Standard of Practice section), but no device-specific PT intervention. Group A will then undergo 4 weeks of device-specific rehabilitation, while group B will not receive any further PT. All participants will then undergo a full gait analysis as well as assessments of function, subjective preferences, neurocognition, cognitive load, and pain after 4 weeks and 8 weeks of powered ankle-foot device use (Figure 1). A comparison between the 2 groups will help evaluate the efficacy of a powered versus passive prosthesis, as well as elucidate the contribution of device-specific effects to rehabilitation-specific effects for individuals with transfemoral limb loss.

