### Planned Statistical Analysis for Pain Outcomes

The following parameters will be measured and statistically compared between baseline (energy storing and returning condition) and each follow-up visit with the powered ankle-foot prosthesis (weeks 4 and 8):

Joint reaction forces on the lower back (L5 and S1) and contralateral (intact) kneesPEQ pain scoresFunctional outcome measures (6MWT, AMPpro, and CHAMP)

Spearman correlations will be calculated to correlate data between pain and lower extremity kinematic and kinetic parameters of interest and pain and functional outcome values across the groups. Linear mixed-effects models will be used to identify statistically significant differences in pain scores and biomechanical variables listed in the previous section for all walking speeds. For example, a linear mixed-effects regression will be used to examine the relationship between peak reaction moments at L5 and S1 and pain for each prosthetic ankle-foot condition. Pair-wise comparisons will be tested for significance using linear contrasts with a Tukey honestly significant difference or by applying a Bonferroni correction, where applicable.

Multiple linear regression will be performed with PEQ pain as the dependent variable. Because of the large number of predictor variables in relation to the number of participants, penalized methods (eg, ridge regression or lasso) will be used to identify variables that contribute the most to the prediction model. Penalized methods add a tuning parameter to the regression model that shrinks the less important coefficients toward 0. Cross-validation will be used to select the best tuning parameter value [62]. The independent variables will be comprised of functional parameters (eg, peak joint reaction forces) and the condition (ankle-foot type and intervention).

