### Power Analysis and Sample Size Estimation

The sample size was based on a power analysis of 3 biomechanical measures (leading limb work, ground reaction force rate, and knee adduction moment rate) and 1 functional outcome (6MWT distance), and 1 subjective outcome (PEQ—utility) obtained from preliminary analyses, with all measurements obtained at baseline and 2 additional measurements over an 8-week period. The sample size was calculated for the group-by-time interaction, which tests the differences in change over time between the study groups. Assuming an α error rate of 5%, Table 5 presents the power achieved for each measurement for 30 participants, 15 (50%) in each group.

**Table 5 table5:** Power analysis and sample size estimation.

Measure	Difference, mean (SD)	Power (N=30)
Leading limb work (J/kg)	0.03 (0.04)	85
Ground reaction force rate (N/kg/s)	15 (26.9)	82
Knee adduction moment rate (N m/kg/s)	1.1 (1.2)	98
6MWT^a^ distance (m)	60 (61)	96
PEQ^b^—utility	8.4 (8.8)	96

^a^6MWT: 6-minute walk test.

^b^PEQ: Prosthesis Evaluation Questionnaire.

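### Visit 2 is timed by weeks of device use in some sections and by completion of a PT programme that only group A has in another, so follow-up times could differ by arm

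*Protocol article*

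**What the plan says.** **Timing by weeks of device use.** The abstract's Methods paragraph says: "Data collection procedures will then be repeated after 4 weeks and 8 weeks of powered ankle use". The Study Overview has all participants assessed "after 4 weeks and 8 weeks of powered ankle-foot device use". Planned Statistical Analysis for Pain Outcomes also names weeks 4 and 8. The power section assumes "all measurements obtained at baseline and 2 additional measurements over an 8-week period".

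**Timing by PT completion.** The section that defines the visit, Data Collection Visit 2, gives no week: "After completion of the device-specific PT program, all participants will undergo data collection on the powered ankle-foot prosthesis". It then adds 4 weeks of home and community use, without further device-specific training, before visit 3.

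**What PT completion means.** The Study Overview plans group A's programme as eight sessions over four weeks. The PT Program Overview gives eight sessions as an average and requires criteria to be met before each move up a level. It adds: "Participants who do not meet the specified criteria will be offered additional PT sessions". The number of such sessions is recorded, but no time or upper limit is given. The Level 4 section says that those who do not meet the criteria to complete the programme "will be offered an additional 8 PT sessions after completion of the study". Group B receives no training beyond the baseline visit.

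**The concern.** The sample size was calculated for the group-by-time interaction with 15 participants per group. That comparison isolates the PT effect only if time means the same thing in both arms. A visit triggered by finishing PT has no counterpart in group B. If the programme overran for some in group A, they would come to visit 2, and then visit 3, with more powered-device use than group B at the same nominal visit. The contrast would then combine PT with length of device use.

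Two outcomes would be affected in a further way. The quality-of-life item and the PEQ Addendum on falls and stumbles both look back 4 weeks. At week 4 that window covers the whole period on the powered device, including first adaptation. At a later visit it leaves out the earliest days, and would do so in group A only.

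**Working it through.** The plan states no figure for visit delay, so there is none to reproduce. The check compares the sections and adds one piece of arithmetic under a stated assumption.

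**1. Do the anchors agree when all goes to plan?** Planned PT length is 4 weeks (Study Overview). Visit 2 by PT completion is then week 4, and visit 3 is 4 + 4 = week 8. Both match the week-based timing.

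**2. Can they separate?** Eight sessions is an average, and progression depends on criteria, so the programme need not last the same time for everyone. Device-specific training is excluded between visits 2 and 3. Additional sessions must therefore come before visit 2 or after visit 3. The Level 4 section places them after the study for participants who do not meet the completion criteria. The PT Program Overview, which covers every level, gives no time. The text therefore leaves three possibilities:

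- extra sessions fit inside the 4 weeks at a higher frequency: shift 0;
- extra sessions come after the study: shift 0;
- extra sessions extend the programme before visit 2: shift above 0, in group A only.

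**3. How large would the third case be?** Assumption: extra sessions run at the planned pace of 8 ÷ 4 = 2 per week. For a participant with k extra sessions, visit 2 falls at week 4 + k/2 and visit 3 at week 8 + k/2. The added device use at visit 2, relative to 4 weeks, is (k/2) ÷ 4 = k/8.

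| Extra sessions k | Visit 2 (week) | Visit 3 (week) | Added use at visit 2 | Visit 2 recall window (weeks) |
|---|---|---|---|---|
| 0 | 4 | 8 | 0% | 0 to 4 |
| 1 | 4.5 | 8.5 | 12.5% | 0.5 to 4.5 |
| 2 | 5 | 9 | 25% | 1 to 5 |
| 4 | 6 | 10 | 50% | 2 to 6 |
| 8 | 8 | 12 | 100% | 4 to 8 |

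Group B would stay at weeks 4 and 8. Any k above 0 also puts visit 3 beyond the 8-week period assumed in the power section.

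**4. From individuals to the arm.** If m of the 15 group A participants each need k extra sessions, the mean shift in group A is (m/15) × (k/2) weeks. For k = 2 this runs from 0 (m = 0), through 1/15 = 0.07 weeks (m = 1), to 1 week (m = 15). The article gives neither m nor k.

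**The case against.** The strongest reply is that the week-based timing is stated repeatedly and consistently, and that the visit 2 sentence is loose wording for the same date, since the programme is planned to last 4 weeks. That stands for a programme that runs to plan. It does not settle what happens when PT overruns, and it does not give the PT-completion anchor a meaning for group B.

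A reader might infer that group A is assessed on reaching the PT criteria, for example the 90% power-trigger accuracy in Table 4, which would be outcome-triggered assessment in one arm. The article does not support this. No section makes visit 2 conditional on meeting the criteria, and the Level 4 section foresees participants who do not meet them and defers their extra sessions to after the study.

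A reader might also infer a bias in favour of PT, or a typical excess of 25 to 50% in device use. Neither can be derived. Extra practice could help group A, but those delayed would be its slower learners. The percentages depend on assumed numbers of extra sessions and would apply only to the individuals delayed.

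The safe-use check at fitting is not an arm-specific problem either. The rule that "the participant will not take the Empower home and will be asked to return for continued supervised use until the participant demonstrates safe use" applies to everyone. It leaves open only when the count of weeks starts.

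Finally, visit windows are often left to the full protocol, and their absence from an article is not held against it. The point rests on two stated anchors that can diverge.

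**Conclusion.** The point holds as an inconsistency that creates a possible difference between the arms in visit timing. One section times visit 2 by an event that group B cannot have; the others time it by weeks of device use. With criterion-based progression and additional sessions of no stated time or limit, visits 2 and 3 could fall later in group A only.

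The shift is zero if PT takes 4 weeks, if extra sessions fit within those weeks, or if they follow the study. Otherwise it is half a week per extra session for the participant concerned, assuming 2 sessions per week. The article does not allow the average shift, or the direction of any resulting bias, to be estimated. The correction is still worth making, because the group-by-time comparison depends on a common time axis and the change is small.

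**What to change.** In the Data Collection Visit 2 and Visit 3 sections, replace the PT-completion anchor with the protocol's own timing: 4 weeks and 8 weeks of powered-device use. Name one starting event for the count, the same in both groups, so that participants held at the safe-use check are handled alike. Apply the same visit window in both groups. Report the PT sessions received and the actual visit times by group, so that any remaining difference in exposure can be seen.

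Separately, the PT Program Overview, the Level 4 section and the Data Collection Visit 2 section must be reconciled by the clinical team on when additional sessions take place relative to visit 2. No view is taken here on which passage is right or how long PT should last.

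The cost is a sentence or two in the visit sections and a visit window. The downside is that some group A participants may be assessed before finishing all PT levels.
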